### Participants and procedure

To ensure the ecological validity of the sample, participants will be recruited through sources that are comparable to how internet interventions are generally promoted in the Netherlands: the *DrinkingLess* website, websites related to alcohol abuse, newspaper articles, a television documentary on CBM for addiction, the website of the ADAPT lab, and word of mouth communication with existing participants. Interested participants are invited to create an account on the intervention website (http://www.test.uva.nl/toptrainingen), after which they read the information letter, a copy of which is automatically sent to them by e-mail. Participants who sign the online consent form then complete a brief screening for eligibility. Participants will be included if they: (a) have an Alcohol Use Disorders Identification Test (AUDIT [30]) score of 8 or above (b) have drunk more than 21 drinks (men) or 14 drinks (women) a week in the past two weeks, as assessed with the Timeline-Follow-Back (TLFB) method (c) are between 18–64 years old (d) have (almost) daily internet access and (e) do not receive professional treatment for problem drinking at the start of the study. Participants with an AUDIT score of >19 receive a message warning them that abrupt abstaining can have mental and physical consequences, and advising them to contact their General Practitioner in case of withdrawal symptoms. Eligible participants then complete the baseline assessment and two modules of *DrinkingLess*. The next day, they are invited to complete the first CBM training session. Participants have three days to complete each session, allowing them to complete the 12 training sessions in about 5 weeks. One day after the last training session, participants are invited to complete the post-intervention assessment. Follow-up assessments are conducted at three, six and twelve months after the intervention. The study has been approved by the Ethics Committee of the psychology department of the University of Amsterdam and registered at the Netherlands Trial register (NTR3875).

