### Primary and secondary outcome measures

The main outcome measure, the change in number of drinks consumed in the past 14 days three months after the intervention compared to baseline, will be assessed using the TLFB method [35]. Secondary outcome measures are: changes in automatic cognitive biases as assessed with the attentional bias, alcohol/no-go and approach bias tasks described above. Generalisation effects of attentional bias and approach bias training to other measures will be assessed with the alcohol Stroop task (described above) and the brief Implicit Association Task (bIAT, [47,48]), which is used to measure the strength of both approach associations and positive (valence) associations with alcohol. In the bIAT, participants are required to decide whether or not the exemplar word in the middle of the screen belongs to one or two focal categories at the top of the screen, by pushing the designated ‘yes’ or ‘no’ buttons (‘e’or ‘i’) on the keyboard. As in the study of Menatti et al. [47], the typical 7 block structure of the IAT was maintained, but with fewer trials per block. In the first block (12 trials) names of alcoholic (wine, beer, vodka) or non-alcoholic drinks (coke, water, juice) have to be classified as either belonging to the category ‘alcohol’ or not. In the second block (12 trials) exemplars have to be classified as either pleasant (funny, cheerful, sociable) or not (nauseous, sad, tired). In the third block (12 trials) and fourth (24 trials), the target (alcohol) and attribute (pleasant) categories are combined. In the fifth block (12 trials), the reversed attribute category, unpleasant, is practiced and then combined with the target category (alcohol) in the sixth (12 trials) and seventh block (24 trials). The approach bIAT follows the same structure, with the attributes ‘approach’ (grab, touch, take) ‘avoid’ (let go, avert, ignore). The order of the two versions of the bIAT, as well as the order of the combined blocks within the bIAT, and the contingency between the response (yes/no) and the buttons (i/e) is counterbalanced across participants. The outcome measure is the standardised difference in latencies (*D* score*)* between the different combined blocks.

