### Sample size

G*Power 3.1.5 [54] was used to calculate the sample size for a power of 0.8 for each main effect or interaction (all Numerator *df* = 1), at an alpha of 0.05. Based on a meta-analysis of internet self-help interventions for problem drinkers a medium effect size (*f* = 0.25) would be expected [2], but the effect size may be reduced by the active control conditions and the two modules of the *DrinkingLess* intervention that all participants receive. A small-to-medium effect size of *f* = 0.15 was therefore specified, for which the required sample size is 351 (see Figure 7).

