### Randomisation

Participants meeting the inclusion criteria will be automatically assigned to one of the 8 intervention conditions with an equal likelihood, using the method of minimisation [55] in order to balance for gender and AUDIT risk level (scores 8–19 versus >19). Participants will be randomly allocated to one of the conditions to which the fewest participants of their gender and AUDIT level have so far been assigned. Intervention allocation will be corrected for excluded participants. Participants will be excluded if (a) they do not complete the baseline assessment including *DrinkingLess*, or (b) if they indicate that they want to discontinue the study.

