### Clinical evaluation

All analyses will be conducted in agreement with the intention to treat principle, as per the CONSORT statement [56]. To that end, missing endpoints will be imputed using the EM algorithm [57]. The main effects and interaction effects of the CBM interventions on the primary and the continuous secondary outcome measures will be analysed with a 2 (attentional bias retraining: active/placebo) × 2 (alcohol/no-go training: active/placebo) × 2 (approach bias retraining: active/placebo) × 2 (time: pre-intervention/3 month follow-up) repeated measures ANOVA.

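### The primary pre/3-month repeated measures ANOVA is an unadjusted change-score test that omits the minimisation factors; ANCOVA on data already collected would be more precise

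*Protocol article*

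**What the plan says.** Under Primary and secondary outcome measures, the primary outcome is "the change in number of drinks consumed in the past 14 days three months after the intervention compared to baseline", measured by TLFB. Under Clinical evaluation, the primary outcome and all continuous secondary outcomes are to be analysed by crossing the three training factors (active/placebo) with "2 (time: pre-intervention/3 month follow-up) repeated measures ANOVA". Baseline drinking therefore enters as one of two repeated responses and not as a covariate. No other term is listed, and covariate adjustment is not mentioned elsewhere in the article.

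Under Randomisation, participants are allocated equally to eight conditions "using the method of minimisation [55] in order to balance for gender and AUDIT risk level", with AUDIT split at 8–19 versus above 19. Neither factor appears in the analysis model.

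Under Sample size, G*Power was used "to calculate the sample size for a power of 0.8 for each main effect or interaction", "at an alpha of 0.05", with f = 0.15, giving N = 351.

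**The concern.** With only two time points, a repeated measures ANOVA has no advantage over a simple analysis of differences: its training-by-time test is the change-score test. A change score subtracts the whole baseline value, whatever the correlation between baseline and follow-up. ANCOVA subtracts only the part that predicts follow-up, estimates the same training effect under randomisation, and has a residual variance that is no larger.

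Allocation is also balanced on two factors that the model then ignores. If those factors predict the analysed quantity, the balance reduces the true variance of the training contrast, but the unadjusted standard error does not reflect the reduction.

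What is at stake is power in a trial sized at exactly 0.80 per effect, for an effect that the article itself expects may be diluted by active controls and by the modules given to everyone. The model is written out in full, so this is a stated choice and not a detail left open for a separate analysis plan.

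**Working it through.** **Inputs from the article.** Eight equal groups, f = 0.15, numerator df = 1, alpha 0.05, power 0.80, N = 351; two time points; minimisation on gender and AUDIT level. **Not given, so assumed over a range:** the baseline/3-month correlation ρ, the SD ratio k (3 months/baseline), and the share of the variance of change that the minimisation factors explain.

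**1. The plan's own figure.** Noncentral F with λ = N·f², df1 = 1, df2 = N − 8. At N = 351, λ = 351 × 0.0225 = 7.90 and power is 0.8002; at N = 350 it is 0.7991. The stated 351 reproduces exactly.

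**2. Equivalence.** On one simulated 2×2×2×2 data set (N = 352), the time-by-training F from the repeated measures model and the F from an ANOVA of change scores were both 7.628767. The identity is algebraic; the simulation only confirms it.

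**3. Relative variance.** In units of the baseline variance:
- change score: 1 + k² − 2ρk
- ANCOVA residual: k²(1 − ρ²)
- difference (change score minus ANCOVA): (1 − kρ)², which is never negative. Apart from the degree of freedom for the covariate, ANCOVA cannot do worse, and it ties only when kρ = 1.

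With k = 1 the ratio ANCOVA/change is (1 − ρ²)/(2(1 − ρ)) = (1 + ρ)/2. For other k:

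| k | ρ = 0.3 | ρ = 0.5 | ρ = 0.7 |
|---|---|---|---|
| 0.7 | 0.42 | 0.47 | 0.49 |
| 0.85 | 0.54 | 0.62 | 0.69 |
| 1 | 0.65 | 0.75 | 0.85 |
| 1.2 | 0.76 | 0.87 | 0.97 |

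Lowest cell: 0.49 × 0.91 / (1 + 0.49 − 0.42) = 0.446/1.07 = 0.42. Highest cell: 1.44 × 0.51 / (1 + 1.44 − 1.68) = 0.734/0.76 = 0.97.

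**4. Power at N = 351 if f = 0.15 is on the SD of change (k = 1).** The noncentrality becomes 7.90 divided by the ratio, with df2 = N − 9.

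| ρ | λ | ANCOVA power | N for 0.80 with ANCOVA |
|---|---|---|---|
| 0.3 | 7.90/0.65 = 12.15 | 0.935 | 229 |
| 0.5 | 7.90/0.75 = 10.53 | 0.899 | 264 |
| 0.7 | 7.90/0.85 = 9.29 | 0.860 | 299 |

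The planned test has 0.80 throughout. These figures adjust for baseline drinks only.

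**5. Omitted minimisation factors.** Suppose the factors are balanced across arms and explain a share R² of the variance of change. The training contrast then varies as (1 − R²), while the unadjusted standard error uses the full variance. A nominal 5% test therefore rejects with probability of about P(|Z| > 1.96/√(1 − R²)). For R² = 0.05 the cut-off is 1.96/0.975 = 2.01, or 4.4%. Simulation (N = 352, four equal strata, 20,000 runs per setting) gave 4.4%, 3.9%, 2.9% and 1.9% at R² of 5%, 10%, 20% and 30%. With the factors in the model the rate was 5.0% to 5.3%.

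**The case against.** The strongest reply is that nothing here is an error. The outcome is defined as change, the hypothesis is a greater decrease under active training, and the planned term tests exactly that. Under randomisation it is unbiased and does not inflate type I error. That stands, and it limits the point to precision. It does not defend the choice, because once baseline is in the model the training coefficient is the same whether the response is change or the 3-month value. ANCOVA therefore answers the same question.

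A second reply concerns size. The gain depends on quantities that the article does not give. It is about 3% in variance at k = 1.2 and ρ = 0.7, and 5% at ρ = 0.9 with equal SDs. For the minimisation factors, stable differences in drinking level cancel in a change score, so the factors must predict change itself; no figure in the article shows that they do. Both remarks stand.

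A reader might infer three stronger points, none of which the article supports:

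- **That the stated power of 0.8 is missed.** This needs f = 0.15 to be scaled on the raw-score SD and ρ to be below 0.5 (with equal SDs, power 0.66 at ρ = 0.3, 0.80 at 0.5 and 0.95 at 0.7). The Sample size section does not say which SD is meant. On the SD of change, which is the declared outcome, 351 is correct whatever ρ is.
- **That the plan would test a training main effect averaged over both time points, halving the effect.** The analysis text speaks of effects on an outcome that is defined as change, and the aims speak of a greater decrease. The natural reading is the training-by-time term.
- **That selection on heavy drinking, "have drunk more than 21 drinks (men) or 14 drinks (women) a week in the past two weeks", undermines the comparison through regression to the mean.** It acts equally in all randomised arms and does not bias the contrast.

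**Conclusion.** The point holds as a loss of precision and as an analysis that does not reflect the allocation scheme. It is not bias, an inflated error rate or a wrong sample size. With equal SDs, ANCOVA has 65% to 85% of the change-score variance for ρ between 0.3 and 0.7. Over the wider grid of SD ratios it has 42% to 97%. If f = 0.15 refers to the SD of change, the planned 0.80 would become roughly 0.86 to 0.94 with the same 351 participants. Leaving out gender and AUDIT level makes the test conservative by an amount that cannot be fixed from the article; 4.4% instead of 5% is an illustration at an assumed 5% of variance explained.

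The direction of the gain is certain and its size is not, because ρ, the SD ratio and the predictive value of the minimisation factors are all assumptions. The change should be made, but the planned test would remain valid without it.

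**What to change.** Restate the primary analysis under Clinical evaluation as ANCOVA: 14-day drinks at 3 months regressed on the three training factors and their interactions, adjusted for baseline 14-day drinks, gender and AUDIT risk level (8–19 versus above 19). Name the three training coefficients as the primary tests, with the factors coded so that each coefficient averages over the other two. Use the same form for the continuous secondary outcomes, each with its own baseline value.

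The cost is a change of wording and three degrees of freedom out of about 340. Baseline TLFB drinking, AUDIT and gender are already required for eligibility or minimisation, so no new data or participants are needed. The sample size of 351 can stand; it would help to add which SD scales f = 0.15.

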### Economic evaluation

The economic evaluation will be conducted from the societal perspective and encompass costs stemming from the intervention, health care uptake and productivity losses due to absenteeism and work cut-back (presenteeism). These costs will be computed from the TiC-P using the full economic cost prices as reported in the pertinent Dutch guideline for assessing health care costs [58]. The costs will be indexed for the reference year 2012. Treatment response will be defined as drinking below the normative cut-off of 21 units per week for men, and 14 units per week for women. The experimental conditions will be compared to the placebo condition to compute the incremental costs and the incremental effects in order to arrive at the incremental cost-effectiveness ratio (ICER). Since the time horizon of this study is less than one year, costs and effects will not be discounted. Employing non-parametric bootstraps, we will simulate 2,500 ICERs and project these on the ICER plane. For medical decision-making purposes, we will also produce the ICER acceptability curve, when the experimental intervention happens to be more effective but also more costly. Sensitivity analyses will be directed at the main cost-drivers with the greatest amount of uncertainty. The same procedure will be used again with quality adjusted life years (QALYs) as the central clinical endpoint. QALYs will be computed from the EQ-5D data while using the Dutch utility tariffs [59].

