## Methods/design

### Trial design

The (cost) effectiveness of attentional bias retraining, alcohol/no-go training, and approach bias retraining will be studied in a 2×2×2 factorial design. This will allow us to explore possible additive or multiplicative effects of different combinations of CBM, as well as the related question to what extent retraining one bias will produce changes in other automatic biases; issues which not only have clinical relevance, but also important theoretical implications (see for example [28,29]). Participants will receive either the active or the placebo version of all three CBM interventions, amounting to eight conditions (see Figure 1). Prior to the training, participants will complete the first two modules of the *DrinkingLess* program [25]*.* Intervention effects will be tested directly after the intervention and 3, 6 and 12 months later. The expected timeline for trial completion and reporting the results is presented in Figure 2.

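### The cost-effectiveness acceptability curve is planned only if the result is more effective and more costly; it should be produced for every comparison, and the economic comparator should be defined.

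*Protocol article*

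**What the plan says.** All the economic statements are in the protocol article, Economic evaluation.

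- Comparison: "The experimental conditions will be compared to the placebo condition to compute the incremental costs and the incremental effects".
- Uncertainty, with no condition on the result: "Employing non-parametric bootstraps, we will simulate 2,500 ICERs and project these on the ICER plane", and "Sensitivity analyses will be directed at the main cost-drivers with the greatest amount of uncertainty".
- Acceptability curve, with a condition: "we will also produce the ICER acceptability curve, when the experimental intervention happens to be more effective but also more costly".
- The effect measure is response (drinking under the sex-specific weekly cut-off). The same procedure is then repeated with QALYs.

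The design facts that bear on precision are elsewhere. Trial design: "Participants will receive either the active or the placebo version of all three CBM interventions, amounting to eight conditions". Randomisation: participants are "automatically assigned to one of the 8 intervention conditions with an equal likelihood". Sample size: the calculation is "for a power of 0.8 for each main effect or interaction (all Numerator *df* = 1), at an alpha of 0.05", and "A small-to-medium effect size of *f* = 0.15 was therefore specified, for which the required sample size is 351".

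**The concern.** An acceptability curve gives, for each value a decision-maker might pay per extra responder or per QALY, the share of bootstrap replicates in which the strategy has positive net benefit. It can be computed wherever the point estimate lies. If a strategy appears dominant, the curve shows how sure that is. If it appears inferior, the curve shows how firmly it can be set aside. Under the stated rule neither reader would get it.

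This is a practical matter here. The article presents the training as low-cost, and the costs counted include health care uptake and lost productivity, so a cost-saving estimate is plausible. Such an estimate would come with no curve.

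The comparator raises a separate question. In an eight-cell factorial, a single placebo condition could mean the cell with placebo for all three trainings, or the placebo side of each training. The two differ in precision and in what they estimate.

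**Working it through.** **1. The plan's own figure.** Inputs from Sample size: f = 0.15, alpha 0.05, power 0.80, numerator df 1; eight cells from Trial design. For the F test with noncentrality f²N and N - 8 denominator df, power is 0.799 at N = 350 and 0.8002 at N = 351. The stated 351 is reproduced.

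**2. Group sizes.** Equal allocation gives 351/8 = 43.9 per cell, and 351/2 = 175.5 on each side of one training's margin. Both are before attrition.

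**3. Precision under the two readings of the comparator.** SE = SD × √(2/n).

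| | One cell v one cell (n = 43.9) | One training's margin (n = 175.5) |
|---|---|---|
| SE, SD units | √(2/43.875) = 0.2135 | √(2/175.5) = 0.1068 |
| 95% half-width, SD units | 1.96 × 0.2135 = 0.42 | 1.96 × 0.1068 = 0.21 |
| 95% half-width, response 30% | 1.96 × √(2×0.3×0.7/43.875) = 19.2 points | 1.96 × √(2×0.3×0.7/175.5) = 9.6 points |
| Same, response 20% to 50% | 16.7 to 20.9 points | 8.4 to 10.5 points |
| Power for d = 0.30 | about 0.29 | 0.80 |

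The SE ratio is √(175.5/43.875) = 2. The response rates are assumptions, as the article gives none. d = 0.30 is 2 × 0.15. The margin column assumes little interaction.

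**4. How often the curve would appear.** Illustration only: independent normal differences in effect (E) and cost (C), in SD units. The chance that the estimate is more effective and more costly is Φ(E/SE) × Φ(C/SE).

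| True E | True C | n = 43.9 per side | n = 175.5 per side |
|---|---|---|---|
| 0 | -0.2 | 0.500 × 0.174 = 9% | 0.500 × 0.031 = 2% |
| 0 | 0 | 0.500 × 0.500 = 25% | 25% |
| 0 | +0.2 | 0.500 × 0.826 = 41% | 0.500 × 0.970 = 48% |
| 0.30 | -0.2 | 0.920 × 0.174 = 16% | 0.998 × 0.031 = 3% |
| 0.30 | 0 | 0.920 × 0.500 = 46% | 0.998 × 0.500 = 50% |
| 0.30 | +0.2 | 0.920 × 0.826 = 76% | 0.998 × 0.970 = 97% |

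Where the true cost difference is near zero, whether the curve appears is largely chance on either reading of the comparator.

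**5. What an estimate outside that quadrant leaves unsaid.** Suppose the estimate itself is +0.30 SD in effect and -0.20 SD in cost, so that the strategy looks dominant and no curve is drawn. With 43.9 per side, the replicates would fall about 0.920 × 0.826 = 76% in the dominant quadrant, 0.920 × 0.174 = 16% in the more effective, more costly quadrant, and 1 - 0.920 = 8% where the strategy is less effective. The plane would show this scatter. It would not give the probability of cost-effectiveness at any stated willingness to pay.

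**The case against.** The strongest reply is that uncertainty is not hidden. The 2,500 replicates go on the plane whatever their quadrant, cost drivers are varied whatever the result, and the whole procedure is repeated for QALYs. The curve is one additional display. This stands, and it rules out the broader inference that economic uncertainty as a whole is reported selectively. It does not remove the point, because a scatter does not give a probability by willingness to pay.

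A reader might also infer that the curve would be built only from replicates in one quadrant. The article says when the curve is produced, not which replicates enter it, so that inference is not supported.

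Nor does the article say that each strategy is set against a single all-placebo cell of about 44. Plural experimental conditions against a singular placebo condition suggest it. Yet the descriptions of the three trainings use the same singular for participants on placebo for one training, which is the factorial margin. Ambiguity is as far as the text goes.

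Finally, the cell contrast and the margin answer different questions. The first compares a given combination with all-placebo; the second averages one training over the others. They coincide only without interaction, and the article states an interest in combined effects. The doubled SE is therefore a reason to define the comparator and show both, not proof that a cell comparison is wrong. Low precision is also not a reporting fault, since the bootstrap would reveal it.

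**Conclusion.** The point holds in a limited form. The article states a result-dependent rule for the acceptability curve, and that rule would withhold the probability of cost-effectiveness when a strategy appears dominant, cost-saving or inferior. Under the assumed effect and cost differences, the condition would be met between 9% and 76% of the time at about 44 per side. That range depends on independent normal differences and on the values chosen.

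The comparator is ambiguous. If it is the all-placebo cell, the SE is twice that of each training's margin: half-widths of about 19 against 10 points at an assumed 30% response, before attrition and with little interaction.

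The consequence is minor. The economic evaluation is a secondary aim, and nothing here touches the primary outcome, the sample size or the clinical analysis.

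**What to change.** Drop the condition. Produce the acceptability curve for every comparison, and for both response and QALYs, from net monetary benefit (willingness to pay × incremental effect - incremental cost) over all 2,500 replicates, whatever the quadrant of the point estimate.

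State which participants form the placebo comparator. Report the active-versus-placebo comparison for each training on the factorial margin, with the eight-cell results alongside so that combinations can be seen and the assumption of modest interaction judged.

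The cost is a change of wording and slightly more analysis, with no new data or participants. The one drawback is that the marginal estimates rest on modest interactions, which is why the eight-cell results should accompany them.
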